## Abstract

**Introduction:**

Capsular group B *Neisseria meningitidis* (MenB) is the most common cause of invasive meningococcal disease (IMD) in many parts of the world. A MenB vaccine directed against the polysaccharide capsule remains elusive due to poor immunogenicity and safety concerns. The vaccines licensed for the prevention of MenB disease, 4CMenB (Bexsero) and MenB-fHbp (Trumenba), are serogroup B ‘substitute’ vaccines, comprised of subcapsular proteins and are designed to provide protection against most MenB disease-causing strains. In many high-income countries, such as the UK, adolescents are at increased risk of IMD and have the highest rates of meningococcal carriage. Beginning in the late 1990s, immunisation of this age group with the meningococcal group C conjugate vaccine reduced asymptomatic carriage and disrupted transmission of this organism, resulting in lower group C IMD incidence across all age groups. Whether vaccinating teenagers with the novel ‘MenB’ protein-based vaccines will prevent acquisition or reduce duration of carriage and generate herd protection was unknown at the time of vaccine introduction and could not be inferred from the effects of the conjugate vaccines. 4CMenB and MenB-fHbp may also impact on non-MenB disease-causing capsular groups as well as commensal *Neisseria* spp. This study will evaluate the impact of vaccination with 4CMenB or MenB-fHbp on oropharyngeal carriage of pathogenic meningococci in teenagers, and consequently the potential for these vaccines to provide broad community protection against MenB disease.

**Methods and analysis:**

The ‘Be on the TEAM’ (Teenagers Against Meningitis) Study is a pragmatic, partially randomised controlled trial of 24 000 students aged 16–19 years in their penultimate year of secondary school across the UK with regional allocation to a 0+6 month schedule of 4CMenB or MenB-fHbp or to a control group. Culture-confirmed oropharyngeal carriage will be assessed at baseline and at 12 months, following which the control group will be eligible for 4CMenB vaccination. The primary outcome is the carriage prevalence of potentially pathogenic meningococci (defined as those with genogroups B, C, W, Y or X), in each vaccine group compared separately to the control group at 12 months post-enrolment, that is, 12 months after the first vaccine dose and 6 months after the second vaccine dose. Secondary outcomes include impact on carriage of: genogroup B meningococci; hyperinvasive meningococci; all meningococci; those meningococci expressing vaccine antigens and; other *Neisseria* spp. A sample size of 8000 in each arm will provide 80% power to detect a 30% reduction in meningococcal carriage, assuming genogroup B, C, W, Y or X meningococci carriage of 3.43%, a design effect of 1.5, a retention rate of 80% and a significance level of 0.05. Study results will be available in 2021 and will inform the UK and international immunisation policy and future vaccine development.

**Ethics and dissemination:**

This study is approved by the National Health Service South Central Research Ethics Committee (18/SC/0055); the UK Health Research Authority (IRAS ID 239091) and the UK Medicines and Healthcare products Regulatory Agency. Publications arising from this study will be submitted to peer-reviewed journals. Study results will be disseminated in public forums, online, presented at local and international conferences and made available to the participating schools.

**Trial registration numbers:**

ISRCTN75858406; Pre-results, EudraCT 2017-004609-42.

Strengths and limitations of this studyThe scale of this carriage study will compensate for the known variation in carriage rates that can occur even when consistent methodology is used across multiple sites. The wide geographical distribution of study sites increases applicability to other settings.Regional allocation of schools to the same study group may increase the power to detect population effects in discrete social networks.The duration of post-immunisation follow-up (6 months) and a single post-immunisation sampling point limits the potential to identify a longer-term or more short-lived reduction in carriage, however, the mobility of school-leavers renders longer-term follow-up during the highest period of acquisition infeasible in this study.This study will inform modelling estimates of potential community-wide impact of adolescent immunisation with either 4CMenB or MenB-fHbp, which are dependent on whether these vaccines induce herd protection.

## Introduction

### Background and rationale

Capsular group B *Neisseria meningitidis* (MenB) accounts for most cases of invasive meningococcal disease (IMD) in the UK, Europe, North America, Australia, New Zealand and many countries in Latin America.^1–3^ Most IMD cases occur in infants and young children, with a smaller peak in incidence in late adolescence. Despite advances in recognition and management, the global case fatality rate remains 9%, with substantial sequelae in many survivors.^1^ While conjugate vaccines that target the polysaccharide capsule of groups A, C, W and Y meningococci are highly effective, a capsule-based vaccine for MenB remains elusive due to poor immunogenicity and potential autoimmunity resulting from homology with surface glycoproteins on human embryonic neural cells.^4^ Consequently the vaccines licensed for the prevention of IMD due to MenB, 4CMenB (Bexsero, GSK) and MenB-fHbp (Trumenba, Pfizer), target subcapsular proteins. These proteins are highly diverse and have variable density of surface expression. Thus, adequate breadth of coverage relies on a multi-component strategy and potential to generate cross-protective vaccine-induced antibodies. The 4CMenB vaccine contains factor H-binding protein (fHbp) from subfamily B/variant 1 fused with the accessory protein GNA2091; Neisserial heparin-binding antigen, Neisserial adhesin A fused with the accessory protein GNA1030 and an outer-membrane vesicle NZ98/254 (PorA 1.4). MenB-fHbp contains two self-lipidated alleles of fHbp, one each from subfamily A/variant 3 and subfamily B/variant 1. 4CMenB and MenB-fHbp were licensed based on safety and immunogenicity data determined by human serum bactericidal antibody activity as an established correlate of protection.^5 6^

In September 2015, the UK introduced a routine 4CMenB infant immunisation programme, in which all infants born after the 1st of May 2015 are eligible to receive a 2+1 schedule of 4CMenB at 2, 4 and 12 months of age. Ten months after introduction, the effectiveness of the 2-month and 4-month doses against all MenB IMD was estimated at 83% with very broad uncertainty (95% CI 24.1–95.2), a result consistent with the estimated breadth of coverage from immunogenicity studies.^3^ At 3 years, expected cases of MenB IMD in vaccine-eligible children reduced by 75%.^7^ Vaccine effectiveness of the 2+1 schedule was 59.1% (95% CI 31.1–97.2) against all MenB IMD and 71.2% against vaccine preventable MenB strains. There are no other vaccine effectiveness studies for either 4CMenB or MenB-fHbp.

Herd protection was not observed or expected from the UK MenB infant programme because carriage is very rare in infants as compared with the peak carriage rates that occur in late adolescence and early adulthood.^8^ The potential for indirect protection to enhance vaccine impact and cost-effectiveness is exemplified by the meningococcal group C conjugate (MCC) vaccine campaign that included children, adolescents and young adults. A reduction in carriage in this targeted population dramatically reduced IMD caused by serogroup C meningococcus (MenC) in all age groups in the UK.^9^ Maintaining this reduction in carriage and therefore MenC IMD in the UK is the primary rationale for an adolescent booster dose of a MenC containing vaccine in early adolescence following infant priming with a single MCC dose given at 12 months of age.

Based on modelling estimates, an infant-only MenB immunisation programme may prevent 26.3% of all-age IMD in the first 5 years after introduction.^10^ If MenB vaccines could reduce meningococcal carriage by 30% and therefore disrupt transmission, a combined infant and adolescent immunisation programme could reduce all-age annual cases by 48.8% at 10 years and 59.7% at 20 years after introduction, enhancing impact and cost-effectiveness.^10^ The impact of 4CMenB immunisation on carriage has been studied in two randomised controlled trials (RCTs) to date. The ‘B Part of It’ cluster-RCT assessed the impact of immunisation with 4CMenB on carriage in 24 269 secondary school students in Australia.^11^ There was no impact on carriage of pathogenic genogroups A, B, C, W, Y or X at 12 months following immunisation. In the UK, 2954 university students were randomised to receive 4CMenB, MenACWY-CRM, or to an active control.^12^ This study showed no effect on the primary outcome of carriage prevalence 1 month after a two-dose schedule of 4CMenB. Using a composite end point of carriage at any timepoint 3–12 months following immunisation, administration of 4CMenB reduced carriage of any meningococcus by 18.2% (95% CI 3.4–30.8) and meningococcus groups B, C, W and Y combined by 26.6% (95% CI 10.5–39.9). This reduction was primarily due to a fall in carriage of meningococci of capsular groups C, W and Y, with a non-significant change in capsular group B meningococcal carriage. Only a minority of students at any institution received the vaccine, which reduced the potential impact of herd protection in the cohort. Studies assessing MenB-fHbp carriage impact are limited to observational reports of several small MenB outbreaks in US universities,^13^ where a number of interventions including mass-immunisation campaigns halted new cases, however these studies were not specifically designed or powered to show an impact of MenB-fHbp vaccine on carriage.

4CMenB and MenB-fHbp may elicit immune responses against non-MenB meningococci and, for 4CMenB, *N. gonorrhoeae*.^14 15^ Vaccine antigens may also be present in commensal *Neisseria* spp. resident in the oropharynx.^15 16^ While cross-protection against meningococci expressing other disease-associated capsular groups is desirable, a broader impact on colonising strains of *N. meningitidis* or potentially protective non-invasive organisms, such as *N. lactamica,* requires surveillance. Unencapsulated meningococci, which are generally non-pathogenic, may have greater surface exposure of vaccine antigens and therefore be more vulnerable to mucosal clearance than the potentially invasive capsule-expressing meningococci. Natural exposure to these bacteria throughout childhood contributes to the development of immunity against hyperinvasive strains.^17^ It is not known whether vaccines that induce immunity to these *Neisseria* spp. may facilitate an unintended niche for pathogenic meningococci.

## Methods

### Study design

The ‘Be on the TEAM’ (Teenagers Against Meningitis) Study is a pragmatic, partially randomised cluster controlled trial that will evaluate the carriage prevalence of pathogenic meningococci in adolescents vaccinated with either 4CMenB or MenB-fHbp, compared with a control group. Participants aged 16–19 years will be enrolled in 16 regions across the UK, with each region allocated to: (1) vaccination at 0 and 6 months with 4CMenB (‘4CMenB Group’); (2) vaccination at 0 and 6 months with MenB-fHbp (‘MenB-fHbp Group’) or (3) an unvaccinated Control Group who will be eligible for deferred vaccination with 4CMenB. Oropharyngeal swab samples (OPSs) will be taken at baseline and at 12 months.

### Primary Objective

To determine the carriage prevalence of culture-confirmed *N. meningitidis* genogroup B, C, W, Y, X (ie, those meningococci possessing genes encoding the capsular polysaccharides corresponding to the respective serogroups) at 12 months after baseline vaccination (6 months following the second vaccine dose) in the 4CMenB and MenB-fHbp Groups compared with the unvaccinated Control Group. The study will not directly compare the 4CMenB Group with the MenB-fHbp Group.

### Secondary Objectives

To determine whether vaccination with either 4CMenB or MenB-fHbp affects the carriage prevalence of:

Genogroup B meningococci.Meningococci of other genogroups and capsule null meningococci.Strains belonging to hyperinvasive meningococcal lineages.All meningococcal strains.Meningococci expressing antigens contained in MenB-fHbp or 4CMenB.Other *Neisseria* spp.

A further secondary objective will be to determine any difference in rates of new acquisition of carriage between groups as defined in the primary and secondary objectives above.

As a stand-alone exploratory objective, this study will also permit an assessment of the impact of the UK adolescent quadrivalent MenACWY vaccination programme on carriage.^18^ This campaign was introduced in 2015 due to a rise in capsular group W meningococcal disease and has high coverage in the school population of prospective participants in this study. ‘UKMenCar4’, an adolescent carriage study across the same study network in 2014–2015 will act as the pre-intervention study.^19 20^ The post-intervention carriage prevalence will be determined by the baseline carriage samples from the Be on the TEAM Study.

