### Study timeline

In order to meet recruitment targets and maximise the interval between immunisation and the final OPS within the structure of the school exam year, the study will recruit across 4 ‘waves’ over 20 months: wave 1 March–May 2018; wave 2 September–November 2018; wave 3 March–May 2019; wave 4 September–November 2019 (figure 2). The academic teaching year runs from September until April or May, depending on local jurisdictions. Recruitment will be balanced between study groups for each of the ‘Spring’ (March–May) and ‘Autumn’ (September–November) recruiting periods in view of expected seasonal variation in carriage. Completion of the final post-vaccination pharyngeal swab collection is expected in early 2021.

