### Randomisation, allocation and blinding

This is an open-label partially randomised study, with group allocation by study site. All schools within the geographical coverage area of each study site will be allocated to the same study arm, both for logistical reasons and because geographical allocation may increase the potential to detect any impact on herd protection. As a post-licensure study, blinded administration and/or placebo will not impact on the outcome of carriage prevalence and would introduce unnecessary cost and complexity to a trial of this scale. The allocation of initial sites was determined prior to the start of the study (figure 1). A capacity assessment stratified sites to either the control arm or immunisation sites depending on existing site expertise and the requirements to maintain equal numbers in each study arm. The immunisation sites were randomised to either the MenB-fHbp Group or the 4CMenB Group. Additional sites may be added during the study and will be pragmatically allocated to a study group to ensure balanced recruitment.

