### Statistical methods

A baseline analysis will occur after wave 2 when the study reaches approximately 50% enrolment. This descriptive analysis of baseline carriage rates will assess the validity of the prospective sample size calculation. There will be no interim analysis of vaccine impact. The principal analysis will be conducted using a modified intention to treat approach, including all participants who have had two throat swabs. Participants will be analysed according to allocated group, regardless of vaccine receipt. Based on previous UK school-based meningococcal carriage studies, the design effect was assumed to be 1.5 in the sample size calculations but will be calculated on the actual data collected.^24 25^

For the primary objective and each of the secondary objectives, carriage rates will be expressed as a mean with two-sided 95% Clopper-Pearson CIs for each group at baseline and at 12 months. The carriage rates in the MenB-fHbp and 4CMenB groups will be compared separately to the Control Group. The OR with two-sided 95% CIs will be calculated using logistic regression via a generalised estimating equations model using an exchangeable working correlation structure. Model covariates will include age, gender, season of recruitment and baseline carriage status a priori. Additional risk factors found to affect carriage at baseline will also be included. Gender and smoking (smoking, home smoking and vaping) are known to affect both vaccine-induced immune responses and meningococcal carriage, and these interactions will be reported regardless of significance. The level of statistical significance will be 0.05. There will be no imputation of missing data for the principal analysis.

Sensitivity analyses will be done for the primary and each of the secondary objectives and will include: analyses without adjustment or inclusion of covariates for completeness and to confirm the results from the primary analyses; a per-protocol analysis of participants who received both vaccine doses in the 4CMenB and MenB-fHbp groups; adjustment for the month of the outcome measure rather than season of recruitment to further investigate the potential effect of seasonality and multivariable imputation for missing data. All variables that will be included in the analysis model will be included in the imputation model and will assume data are missing at random.

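### The MenACWY before/after evaluation uses all baseline swabs as its post-programme sample, though many are taken after MenB vaccination has begun in the same region

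*Protocol article*

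**What the plan says.** The protocol article, under Secondary Objectives, introduces the evaluation thus: "As a stand-alone exploratory objective, this study will also permit an assessment of the impact of the UK adolescent quadrivalent MenACWY vaccination programme on carriage". UKMenCar4, run in 2014–2015 on the same study network, supplies the data from before the programme. For the period after it: "The post-intervention carriage prevalence will be determined by the baseline carriage samples from the Be on the TEAM Study". Neither sentence limits the sample by wave or arm.

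Three other sections bear on when those swabs are taken:

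- Study timeline: four waves, the first two in spring and autumn 2018, then "wave 3 March–May 2019; wave 4 September–November 2019".
- Randomisation, allocation and blinding: "All schools within the geographical coverage area of each study site will be allocated to the same study arm". One reason given is that "geographical allocation may increase the potential to detect any impact on herd protection".
- Interventions: vaccine-group participants are dosed at 0 and 6 months. Controls are offered 4CMenB once their 12-month swab has been taken.

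Background and rationale describes a composite-endpoint reduction under 4CMenB in an earlier trial in UK university students: "This reduction was primarily due to a fall in carriage of meningococci of capsular groups C, W and Y".

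**The concern.** A before/after evaluation needs a post-programme sample that differs from the earlier one in the programme of interest and, as far as possible, in nothing else. Here a second meningococcal vaccine is being introduced into the same regions while the sample is still being collected. A baseline swab is unaffected by the participant's own MenB vaccination, but not necessarily by that of earlier participants nearby. The trial allocates by region partly because such indirect effects might occur.

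If they do occur, and reach groups C, W or Y, the later baseline swabs will show lower carriage for a reason unrelated to MenACWY. The evaluation as defined would attribute that part of the fall to the national programme.

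**Working it through.** **Figures in the plan.** The article states no figure for this evaluation. The per-arm sample size, which sets the two-thirds share of swabs from vaccine regions, does reproduce. For 3.43% against 2.401% (a 30% reduction), two-sided 0.05 and 80% power, n = 4,196. Then 4,196 × 1.5 / 0.8 = 7,868, against the stated 8,000, where power is 80.7%.

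**Step 1: which baseline swabs follow local MenB vaccination.** Dates are from Study timeline; the schedule and deferred offer are from Interventions.

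| Wave | Baseline swabs | Vaccine regions | Control regions |
|---|---|---|---|
| 1 | Mar–May 2018 | not yet begun | not begun |
| 2 | Sep–Nov 2018 | begun: wave 1 first doses about 6 months earlier | not begun |
| 3 | Mar–May 2019 | begun | possibly: wave 1 controls reach 12 months |
| 4 | Sep–Nov 2019 | begun | begun where the deferred offer was taken up |

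Wave 1 is treated as unexposed, although its later swabs may follow the first doses by some weeks.

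**Step 2: exposed share f.** Statistical methods says: "A baseline analysis will occur after wave 2 when the study reaches approximately 50% enrolment". So about half of enrolment falls in waves 3 and 4. Two of the three equal arms are vaccine arms.

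- Waves 3–4 in vaccine regions: f = 0.5 × 2/3 = 1/3, or 8,000 of 24,000.
- Adding wave 2, with equal waves: f = 0.75 × 2/3 = 1/2, or 12,000.

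Both leave out control-region swabs exposed through deferred vaccination, because take-up is not given.

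**Step 3: the programme effect.** Sample size gives 4.2% before the programme and 3.43% after an assumed 50% fall in W and Y. The drop is 0.77 points, so implied W/Y carriage is 2 × 0.77 = 1.54% before and 0.77% after.

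**Step 4: bias.** Let h be the relative indirect reduction in exposed swabs. The documents give no h, so a range is assumed. Apparent W/Y reduction = 1 − 0.5 × (1 − f·h).

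| Assumed h | f = 1/3 | f = 1/2 |
|---|---|---|
| 0 | 50.0% | 50.0% |
| 5% | 50.8% | 51.25% |
| 10% | 51.7% | 52.5% |
| 15% | 52.5% | 53.75% |
| 30% | 55.0% | 57.5% |

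At the top of the range (f = 1/2, h = 30%) the shift in W/Y prevalence is 0.77 × 0.15 = 0.12 points. For scale, the 95% half-width for W/Y from 24,000 swabs, assuming the design effect of 1.5 applies, is 1.96 × √(0.0077 × 0.9923 × 1.5 / 24,000) = 0.14 points.

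If wave 4 control swabs were also fully exposed, f would be 14,000/24,000 = 0.58 and the top reading 1 − 0.5 × (1 − 0.583 × 0.30) = 58.75%.

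**Step 5: what a restricted sample keeps.** With equal waves there are 2,000 swabs per arm per wave. Wave 1 in all regions gives 6,000, and control regions in waves 2 and 3 give 4,000, for a total of 10,000. The standard error rises by √(24,000/10,000) = 1.55. If wave 3 controls must also go, 8,000 remain and the factor is √3 = 1.73.

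**The case against.** The strongest reply is that this is one data-source sentence for an exploratory objective in a condensed article. No model or pooling rule is given, and separation by wave and arm may be in the full protocol or analysis plan. That stands as far as it goes: a reader might infer that the article commits to simple pooling, and it does not say so. It does fix the sample, however, and that sample carries no restriction.

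A reader might also infer that any MenB herd effect would be booked as MenACWY impact. The documents do not support this. The effect is diluted by the unexposed swabs, and a fall in group B would not enter a contrast on C, W and Y. For the same reason it misleads to set the bias against the 0.77-point drop using the five-genogroup composite. That gives 0.06 to 0.34 points at one third exposed, up to 45% of the drop, but only by counting group B carriage that MenACWY does not target.

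Nor is the direction certain. Background and rationale leaves open whether these vaccines could make room for pathogenic meningococci, and it reports no carriage impact in the large Australian cluster trial. The C, W and Y finding in university students came from receiving 4CMenB, on a composite endpoint in a trial whose primary outcome was null. It is not evidence of an indirect effect in later entrants.

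Exposure may be thin as well. Patient and public involvement expects about 48,000 students to be reached for 24,000 enrolled, roughly half of those year groups. Nothing says that later waves return to the same schools. All of this argues for a small h, not for ignoring the route.

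**Conclusion.** The point holds as a conditional one. The article's post-programme sample includes swabs taken after MenB vaccination had begun locally: between one third and one half of the total in vaccine regions, plus an unknown number of late control-region swabs. If there is an indirect reduction in C, W or Y, the MenACWY effect is overstated. A true 50% W/Y fall would read 50.8% to 55% with one third exposed, or 51.25% to 57.5% with one half, for assumed indirect reductions of 5% to 30%. The 30% end is an upper scenario, since it sets the indirect effect equal to the full effect the trial is powered to detect. With no indirect effect there is no bias.

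These figures assume equal waves within each half of recruitment, a two-thirds vaccine-region share in every wave, and the article's own 50% W/Y fall as the truth. The objective is exploratory, and the primary and secondary vaccine comparisons are not touched. This is a worthwhile refinement, not a threat to the trial.

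**What to change.** In the analysis plan for this objective:

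1. Classify each baseline swab by whether MenB vaccination, trial or deferred, had already begun in its region.
2. Include that indicator in the MenACWY model and compare with UKMenCar4 within the same regions.
3. Report prevalence by wave and arm.
4. Beside the all-swab estimate, give one from swabs taken before local MenB vaccination: wave 1 everywhere, plus control-region swabs before deferred vaccination. Keeping every control-region swab, or wave 2 swabs from vaccine regions, would not give an unexposed set.

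No new data are needed. The cost is precision: about 10,000 of 24,000 swabs remain and the standard error rises by about 55%. The W/Y half-width goes from about 0.14 to 0.14 × 1.55 = 0.21 points, wider than the 0.12-point bias at the top of the one-half-exposed range, so the restricted estimate should not replace the all-swab one with the exposure term. The restricted set is also mostly spring swabs (8,000 of 10,000 with equal waves, against half overall). Because the article expects seasonal variation in carriage, season should be in the model.
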